### Interventions

#### Control group

Patients randomised to the control group will receive standard care according to the local protocol. One month prior to surgery, patients are invited to the preoperative outpatient clinic, where they are individually counselled by a physician and a nurse practitioner. They are also handed information brochures after a nurse-led group session during which they receive information on the CABG care process at our hospital.

After surgery, patients have an in-hospital physiotherapist consultation. Before discharge, a resident or nurse provides brief information about the permitted level of physical activity and the medication schedules and answers remaining questions patients might have. Outpatient postoperative follow-up is scheduled for 6 weeks after discharge. Structured guidance to improve general condition and strength by a physiotherapist is offered (cardiac rehabilitation). Patients have no planned care in the first 6 weeks after discharge.

#### Intervention group

Aside from standard care as described in the previous section, patients in the intervention group will have access to educational videos and will be invited to two video consultations. Access will be granted through a link sent by email. The educational videos will be made available directly after randomisation for the duration of the study, via a secure online portal. The portal provides an orderly index in which patients can navigate by means of preformulated questions stratified in three categories: treatment, recovery and healthy living (Fig. 1). Each question will be accompanied by an educational video, which provides information and practical advice if applicable (Fig. 2).

**Fig. 1 Fig1:**
[figure not shown]
Welcome screen of the eHealth programme with stratification of topics on which patients can find information: treatment (*Behandeling*), recovery (*Herstel*) and healthy living (*Gezond leven*)

**Fig. 2 Fig2:**
[figure not shown]
Overview of the portal for the eHealth programme

The aim of the videos is to prepare patients, and their caregivers and family members for the surgery and offer guidance during the recovery process. The videos were developed by the Dutch Heart Foundation and were made available specifically for this study. Videos contain spoken text with animations (Figs. 3 and 4); all information is in Dutch. A nurse practitioner experienced in care for cardiothoracic surgery patients will conduct the video consultations with patients on their recovery and any complaints. Supervision will be provided by a cardiothoracic surgeon. The nurse practitioner will be told the study’s aim is to ‘improve the current follow-up procedure’ and that he or she will therefore be blinded for the specific outcomes.

**Fig. 3 Fig3:**
[figure not shown]
Still from the video ‘What is coronary artery bypass surgery?’

**Fig. 4 Fig4:**
[figure not shown]
Still from the video ‘How to prepare for coronary artery bypass surgery?’

### Outcomes

#### Primary outcome measure

The primary outcome is the volume of unplanned healthcare utilisation (resources used per patient). Healthcare utilisation is defined as a composite endpoint of all emergency department visits, outpatient clinic visits, rehospitalisation, patient-initiated telephone consultations with a physician or nurse, and visits to a general practitioner, allied health professionals and psychologists.

An adaptation of the Institute for Medical Technology Assessment Medical Consumption Questionnaire (iMCQ) will be used to determine the volume of healthcare utilisation and the reasons thereof. This generic questionnaire aims to determine the costs of healthcare based on care consumption and is applicable to the Dutch healthcare system [10]. The questionnaire answers will result in absolute frequencies of visits for the relevant care activities. When patients report the use of healthcare, their healthcare provider will be contacted to validate the date and the reason for the healthcare encounter. This information will be crossvalidated with the subjects’ self-reports.

#### Secondary outcome measures

Secondary outcome measure are defined as the individual care activities of unplanned healthcare utilisation, a composite endpoint of consultations with a general practitioner, allied health professionals and psychologists plus patient-initiated telephone consultations with a physician or nurse, and a composite endpoint of in-hospital care (emergency department visits, outpatient clinic visits, rehospitalisation).

#### Tertiary outcome measures

Tertiary outcome measures are the patients’ quality of life and their mental and physical status. To assess these domains, the 36-Item Short Form Health Survey (SF-36) [11], the anxiety subscale of the Hospital Anxiety and Depression Scale (HADS) [12] and an adaptation of the Recovery Index-10 (RI-10) [13] will be used at different time points during follow-up (Tab. 2).

**Table 2 Tab2:** Schedule of enrolment, interventions and assessments

	Time point^a^							
	Enrolment	Surgery	Follow-up					
Variable	*T*_*0*_		*T*_*1*_	*T*_*2*_	*T*_*3*_	*T*_*4*_	*T*_*5*_	*T*_*6*_
**Enrolment**								
– Eligibility screening	X							
– Informed consent	X							
– Allocation	X							
**Interventions**								
*Intervention group*								
– Standard care	X	X	X	X	X	X	X	X
– Online educational videos	X		X	X	X	X	X	X
– Video consultation				X		X		
*Control group*								
– Standard care	X	X	X	X	X	X	X	X
**Assessments**								
*Primary and secondary outcome measures*								
– Healthcare utilisation (iMCQ)						X		
*Tertiary outcome measures*								
– Quality of life (SF-36)	X							X
– Anxiety (HADS subscale)	X		X	X	X	X		
– Recovery (RI-10)			X	X	X	X		
*Process measures*								
– Patient satisfaction (satisfaction questionnaire)							X	
– Use of intervention (internet usage log)	X	X	X	X	X	X	X	X
*Patient and procedural data*								
– Sociodemographic data (iMCQ)	X							
– Patient characteristics (patient files)	X							
– Follow-up data (patient files)						X		

*iMCQ* Institute for Medical Technology Assessment Medical Consumption Questionnaire, *SF-36* 36-Item Short Form Health Survey, *HADS* Hospital Anxiety and Depression Scale, *RI-10* Recovery Index-10

^a^T_0_: 1 month before surgery; T_1_: 1 week after surgery; T_2_: 2 weeks after surgery; T_3_: 3 weeks after surgery; T_4_: 6 weeks after surgery; T_5_: 2 months after surgery; T_6_: 6 months after surgery

The SF-36 is routinely used at our facility and has been validated in multiple patient populations, including cardiac surgery patients [14–18]. This questionnaire assesses health-related quality of life in the previous 4 weeks. The HADS questionnaire is widely validated and is most commonly used to assess depression or anxiety. The RI-10 is a short, Dutch-language, 10-item questionnaire measuring postoperative domains on a 5-point scale over the last 7 days. It has been validated in gynaecology patients, but the general nature of the questions suits our patient population [19].

#### Process measures

The performance of the eHealth strategy on several domains will be structurally evaluated using qualitative and quantitative measures [20, 21]. The process evaluation will assess participant attitude, eligibility, access, usage and engagement of the eHealth strategy (Tab. 3), in order to make recommendations on the development and subsequent implementation of eHealth strategies. Data will originate from the internet usage log of the portal and the patient satisfaction questionnaire.

**Table 3 Tab3:** Process evaluation of eHealth strategy

Domain *method of collection*	Portal	Video consultation
Eligibility *logistic data*	Number of patients not eligible for inclusion due to technological limitations (e.g. no computer access, digital illiteracy)	
Access *logistic data*	Number of patients that received access to an account	Number of patients that were invited via email
Usage *internet usage log*	Number of patients that logged in during the study period	Number of patients that completed the planned video consultation
	Time points at which patients logged in	Number of patients that experienced technical errors and the reasons thereof (e.g. magic link not working, bad quality of video connection)
	Average session length	
Engagement *internet usage log*	Number of videos started and completed during each visit	Average session length
	Number of times each video was started and completed	
Participants attitude *questionnaire*	Assessment of the portal/software (e.g. accessibility, interface, navigation) and reasons for not using the portal/software (if applicable)	
	Evaluation of content (comprehensible, use of words, useful)	Number of patients that deem video consultation a meaningful addition to standard care
	Number of patients that would recommend the content as a source of information to family members or other patients	

#### Patient and procedural data

Patient characteristics (age, sex, comorbidities), procedural characteristics (in-hospital complications, length of stay, duration of surgery), follow-up data (mortality, reoperations, deep sternal wound infections, stroke, recurrent myocardial infarction within 30 days) and sociodemographic information will be collected and analysed to provide insight into our patient population and to adjust endpoints if necessary. Patient, procedural and follow-up data are routinely collected at our facility and are defined by the Netherlands Heart Registry [22]. Sociodemographic data are part of the iMCQ.

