**Objectives:**

We aim to evaluate whether the use of an eHealth programme can reduce unplanned healthcare utilisation and improve mental and physical health in the first 6 weeks after discharge in patients who underwent CABG. In addition, patient satisfaction and use of the eHealth programme will be evaluated.

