## Discussion

The IMPROV-ED trial is of clinical significance for several reasons. First, we will evaluate the influence of an eHealth strategy on healthcare utilisation, anxiety, quality of life and recovery. Positive results will yield a new postoperative protocol that will lead to better patient outcomes and reduced costs [25]. In addition, the process and patient satisfaction evaluation will show the readiness of CABG patients for structured eHealth initiatives and will evaluate the currently used content and mode of administration, given the broad applicability of eHealth in general and the multitude of devices available [26–28]. Second, the control arm of the trial will provide the first detailed insight into unplanned, transmural healthcare utilisation in the early postoperative period after CABG and will thereby show how to further improve post-CABG protocols, aside from eHealth, through multidisciplinary regional collaboration.

eHealth strategies in CABG patients have been successfully applied to guide secondary prevention [29], to improve recovery [30, 31], and to assess physical functioning and quality of life [32–34]. Although evidence on the effect of eHealth on healthcare utilisation in CABG patients is minimal, it is reasonable to expect a positive effect based on reduction of healthcare utilisation by eHealth strategies in other populations [8, 23, 35, 36]. According to post-CABG protocols, patients are expected to adopt new behaviours (e.g. relieve stress on the sternum, gradually increase in physical exercise, follow healthy diet) and to deal with the emotions and worries that go with cardiac surgery through self-management, and, thus, to take responsibility for their own recovery [6]. eHealth has shown to be a useful method for patients to enhance their self-management through better understanding of their disease, increased independence and improved acceptance to adhere to lifestyle advice [37]. The educational videos in our eHealth strategy facilitate self-management. By means of video consultation, the physician can guide and supervise the patient’s progress and maintain a good patient-physician relationship, which has been shown to enhance the patient’s self-management skills [37].

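### Clinical events have only a descriptive or adjusting role, and a possible 30-day limit, beside a 6-week utilisation count, so a lower count cannot be read reliably as benefit

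*Protocol article*

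**What the plan says.** The Protocol article, Primary outcome measure, states: "The primary outcome is the volume of unplanned healthcare utilisation (resources used per patient"). It is a composite of emergency visits, outpatient visits, rehospitalisation, telephone consultations started by the patient, and visits to general practitioners, allied health professionals and psychologists. The Objectives place the hoped-for reduction "in the first 6 weeks after discharge in patients who underwent CABG". Table 2 schedules the utilisation questionnaire once, at T4, which its footnote defines as "6 weeks after surgery".

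The clinical events appear under Patient and procedural data as "follow-up data (mortality, reoperations, deep sternal wound infections, stroke, recurrent myocardial infarction within 30 days"). The stated purpose of the data in that section is "to provide insight into our patient population and to adjust endpoints if necessary". The sections on primary, secondary and tertiary outcomes name no clinical event apart from rehospitalisation as an item of utilisation. Table 2 has a row for "Follow-up data (patient files"), marked at T4.

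Other parts of the plan bear on patients' health. The questionnaire is used "to determine the volume of healthcare utilisation and the reasons thereof", and the provider is contacted to confirm date and reason when a patient reports care. The secondary outcomes include each care activity and a separate in-hospital composite. Anxiety (HADS) and recovery (RI-10) are measured to T4, and quality of life (SF-36) at T6.

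The Discussion expects that "Positive results will yield a new postoperative protocol that will lead to better patient outcomes and reduced costs".

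**The concern.** The primary outcome scores every avoided contact as a gain, whatever the reason for the contact. A programme of education and video consultation could lower the count in several ways: fewer needless visits, earlier detection of problems, or some needed visits delayed or not made. The count alone does not say which of these happened.

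The data best placed to help are clinical events ascertained independently of whether the patient reports using care. The plan collects such data but gives them the role of describing the population or adjusting endpoints, and the stated window may stop before the utilisation window does. A lower count could then be reported as a benefit with no by-arm view of deaths, reoperations, deep sternal infections, strokes and infarctions over the same period.

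The adjusting role has its own problem. The intervention arm gets the videos directly after randomisation, about a month before surgery. The listed events therefore all arise after allocation and could be affected by it. Adjusting the endpoints for them could remove part of the treatment effect or bias it.

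**Working it through.** **1. The windows.** Inputs: 30 days (Patient and procedural data); 6 weeks = 42 days (Objectives; Table 2 footnote for T4). The article does not say where the 30 days start.

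- Both clocks starting on the same day: 42 − 30 = 12 days; 12/42 = 28.6%, about 29%.
- Events counted from surgery and utilisation from discharge: the gap is 12 days plus the postoperative stay, whose length is not given.
- 30 days governing recurrent infarction only: there is no stated limit for the other events, and the T4 file review may already cover 6 weeks after surgery.

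So 29% depends on how the list is read and on a common starting day.

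**2. What each source shows about needed care.**

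| Source | What it shows | What it leaves open |
|---|---|---|
| Encounter reasons, confirmed by the provider | Why reported care was used | Care needed but not sought has no encounter |
| In-hospital composite and single activities | A shift from calls to admissions or emergency visits | A fall has the same competing explanations as the primary count |
| RI-10 and HADS anxiety to T4 | Self-reported recovery and anxiety | Reassurance can improve both, justified or not |
| SF-36 at T6 | Later quality of life | Responders only |
| Events from patient files | Events without reliance on self-report | No outcome role; window unclear |

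**3. The plan's sample size.** Inputs (Sample size calculation): d = 0.35, α = 0.05 (taken as two-sided), power 0.80.

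- Normal approximation: n per arm = 2(1.960 + 0.842)²/0.35² = 15.70/0.1225 = 128.2, rounded up to 129; total 258.
- Exact t-test: 130 per arm, total 260, which is the plan's figure.

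The plan then sets 280, or 140 per arm. This point does not change that number.

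**4. What 140 per arm could show about events.** The article gives no event rates, so control rates p of 2%, 5%, 8% and 10% are assumed.

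- Half-width of the 95% CI for the risk difference, equal rates: 1.96 × √(2p(1 − p)/140). At p = 0.05: 1.96 × √(0.095/140) = 1.96 × 0.02605 = 0.051.
- Power to detect a doubling: Φ[(p − 1.96 × SE₀)/SE₁], with SE₀ pooled and SE₁ unpooled. At 5% against 10%: SE₀ = √(2 × 0.075 × 0.925/140) = 0.03148; SE₁ = √((0.0475 + 0.09)/140) = 0.03134; (0.05 − 0.0617)/0.03134 = −0.373; power 0.354.

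| Assumed control rate | CI half-width (percentage points) | Power for a doubling | n per arm for 80% power |
|---|---|---|---|
| 2% | 3.3 | 16% | 1141 |
| 5% | 5.1 | 35% | 435 |
| 8% | 6.4 | 54% | 258 |
| 10% | 7.0 | 65% | 199 |

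A by-arm table is therefore a descriptive safety reading. It could not rule out a moderate excess.

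**The case against.** The strongest reply is that the plan already gives much of the information. A stroke, reoperation or deep infection presenting between day 30 and week 6 would normally bring an emergency visit or a readmission. If reported, it raises the primary count, enters the in-hospital composite and carries a confirmed reason. Fewer calls with more rehospitalisations would show in the secondary outcomes. The video consultations also add contact with an experienced nurse practitioner under a surgeon's supervision, which may bring problems to light sooner. The Discussion sentence is an expectation and not a decision rule. The event data are to be analysed, so a by-arm table is not excluded, and a fuller protocol or analysis plan may contain one.

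Most of this stands. A reader might infer that event capture certainly ends at day 30, or that a fall in utilisation cannot be told apart at all from missed care. The documents support neither. The 30-day phrase may belong to recurrent infarction alone, Table 2 places the file review at 6 weeks, and reasons, composites and health questionnaires each help to separate the explanations. Nor does the article show that late events would go uncounted: those that led to reported care are counted.

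Two things are not answered. Reasons exist only for care that was used and reported, so needed care never sought, or a death without contact, leaves no trace in the utilisation data. And the role of the events is stated in the article: description and adjustment. That is a choice the text makes, not a detail left for later.

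**Conclusion.** The point holds in a limited form. The listed events have no outcome role beside a primary endpoint in which fewer contacts count as success, and their window is either shorter than the utilisation window or unclear. The other measures narrow the gap without closing it, so a lower count is not by itself reliable evidence of benefit.

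The size is 12 of 42 days (29%) if the 30 days govern the whole list and both windows start on the same day. The gap is larger by the length of stay if utilisation is counted from discharge and events from surgery. If the limit applies to infarction only, what remains is the role of the events and an unclear window. The power range of 16% to 65% rests on assumed control rates of 2% to 10%, since the article gives none.

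A reader might also infer that the article must extend event follow-up to 6 months, make its conclusion conditional on the event comparison, or rank deaths as the worst outcome. None of these follows: Table 2 schedules no file review at T6, the comparison is too imprecise to act as a condition, and the analysis of deaths may properly sit in the analysis plan.

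**What to change.** - Reconcile Patient and procedural data with Table 2. State one window for all listed events, running to the end of the 6-week utilisation window and starting on the same day. Use the file review already planned at T4; if the window runs from discharge, time that review to reach its end. The 30-day registry figures can be kept as well.
- Name these events as a descriptive between-arm safety outcome: counts per arm, risk difference and 95% CI, reported beside the primary result with deaths shown.
- Do not use these post-randomisation events as adjustment covariates; limit adjustment to variables fixed before randomisation.

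The cost is small: a stated cut-off in a review that is already scheduled, one more table, and no change to 280 patients. The downside is wide intervals, about 3 to 7 percentage points either side at the assumed rates. The article should say that the comparison is not powered and that an interval including zero does not establish safety.

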### Recruitment and allocation

All patients planned for preoperative outpatient counselling for CABG will be contacted by telephone in the week of their scheduled appointment. Patient eligibility for the trial will be assessed according to prespecified inclusion criteria (Tab. 1). Eligible patients will be informed about the study protocol by one of the investigators after their scheduled appointment. If the patient is willing to participate, the informed consent form is signed. At inclusion, patients are randomised to either the intervention or control group in a ratio 1:1 using block randomisation, with a block size of four.

**Table 1 Tab1:** Eligibility criteria

Criterium	
1	>18 years of age planned for elective, isolated CABG/OPCAB
2	Sufficient computer knowledge, and internet access. Children can assist, but patients should be able to access their own email and navigate the internet to use the provided eHealth strategy
3	Access to computer with internet connection and webcam or build-in camera
4	Comply to minimal specifications for use of video consultation:
	– PC/laptop: Windows 7 or 10 with Chrome or Firefox browser
	– Android tablet: at least Nougat software installed and use of Chrome browser
	– Apple iPad: at least iOS 12.3.4
5	Ability to speak, read and interpret the Dutch language
6	Provide informed consent

*CABG/OPCAB* coronary artery bypass grafting/off-pump coronary bypass

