### Statistical considerations

#### Data analysis

Descriptive statistics will be used to summarise baseline characteristics of the study population. Healthcare utilisation will be expressed as mean ± standard deviation (resource use per patient) and absolute and relative frequencies (users per resource). Mann-Whitney U test and Fisher exact test will be used to compare the intervention and control group. Multivariate regression analysis will be performed to adjust the outcomes for confounding factors based on univariate analysis (*p* < 0.1), literature review and expert opinion.

The primary analysis will be an intention-to-treat analysis. In the secondary analysis, we will compare the control group with the intervention group that used the educational videos at least once and completed the video consultations (‘users only’). A *p*-value <0.05 will be considered statistically significant and all analyses will be performed using SPSS 25 (SPSS Inc., Chicago, IL, USA).

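### The adjustment rule lets post-randomisation events (complications, length of stay, reinfarction, wound infection) into the treatment model, so the adjusted result could be biased, and the text does not say which result decides

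*Protocol article*

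**What the plan says.** Protocol article, Patient and procedural data: one sentence covers patient characteristics, sociodemographic information and two further groups. One group is given as "procedural characteristics (in-hospital complications, length of stay, duration of surgery"). The other, named separately, is "follow-up data (mortality, reoperations, deep sternal wound infections, stroke, recurrent myocardial infarction within 30 days"). The sentence states a joint purpose for all four: they "will be collected and analysed to provide insight into our patient population and to adjust endpoints if necessary". Nothing separates variables known at baseline from those that arise later, and nothing says when adjustment becomes necessary.

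Protocol article, Data analysis: "Multivariate regression analysis will be performed to adjust the outcomes for confounding factors based on univariate analysis", with a threshold of p<0.1, and also on literature review and expert opinion. The same section names the Mann-Whitney U and Fisher exact tests for the group comparison, makes intention-to-treat primary, and adds a secondary users-only comparison.

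On timing, Recruitment and allocation states: "At inclusion, patients are randomised to either the intervention or control group in a ratio 1:1 using block randomisation, with a block size of four". Control group states: "One month prior to surgery, patients are invited to the preoperative outpatient clinic". Intervention group states: "The educational videos will be made available directly after randomisation for the duration of the study".

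**The concern.** In a 1:1 randomised comparison, a variable that arises after allocation cannot be a confounder of the treatment effect. It can be a mediator, in which case adjusting for it removes the part of the effect that runs through it. It can also be a collider: affected by treatment and sharing an unmeasured cause with the outcome, so that adjusting for it creates an association that treatment did not cause.

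Both are conceivable here. The Introduction expects utilisation to fall by way of better health and quicker recovery, and complications or length of stay are plausible markers of that route. The primary composite counts rehospitalisation, emergency visits and outpatient visits, which a wound infection, reoperation, stroke or infarction can bring about. Such events predict the outcome, so a univariate screen against the outcome is likely to select them. At stake is whether the adjusted estimate still answers the intention-to-treat question, and which estimate readers will be given as the trial's answer.

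**Working it through.** **1. Order of events.** Randomisation takes place at inclusion, at the preoperative clinic visit about one month before surgery. The videos open at once. Duration of surgery, in-hospital complications, length of stay and all the listed follow-up events come later. Table 2 collects the follow-up data at T4, the same time point as the utilisation questionnaire. Age, sex, comorbidities and the T0 sociodemographics are the listed items fixed before allocation.

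**2. The plan's own figure.** For d = 0.35, two-sided α = 0.05 (sidedness is not stated; a one-sided calculation gives 202 and does not match) and power 0.80:

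n per arm = 2 × (1.960 + 0.842)² / 0.35² = 128.1, rounded up to 129, total 258.

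The t-test version gives 129.1, rounded up to 130, total 260, as stated. At the planned 140 per arm, power is Φ(0.35 × √70 − 1.960) = Φ(0.968) = 0.83. The sample size is an unadjusted two-group calculation and is not in dispute.

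**3. Adjusting for a mediator (assumed strengths).** Let A be the arm, M a post-randomisation variable with within-arm SD 1, and s the share of the effect that runs through M:

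- M = −(0.35 s / 0.5) A + noise
- Y = −0.35 (1 − s) A + 0.5 M + error of variance 0.75, so the within-arm variance of Y is 0.25 + 0.75 = 1

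The total effect is −0.35 (1 − s) − 0.35 s = −0.35 for every s. The coefficient of A after adjusting for M is −0.35 (1 − s). Simulation, 140 per arm, 4,000 runs each:

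| s | shift in M (SD) | formula | simulated adjusted estimate | adjusted rejection rate | unadjusted rejection rate |
|---|---|---|---|---|---|
| 0 | 0 | −0.35 | −0.35 | 0.92 | 0.84 |
| 0.25 | −0.175 | −0.2625 | −0.26 | 0.70 | 0.82 |
| 0.50 | −0.35 | −0.175 | −0.18 | 0.40 | 0.84 |
| 0.75 | −0.525 | −0.0875 | −0.09 | 0.12 | 0.83 |
| 1.00 | −0.70 | 0 | 0.00 | 0.05 | 0.84 |

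The unadjusted estimate stayed at about −0.35 throughout.

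**4. Adjusting for a collider (assumed strengths).** The true effect on Y is 0. M and Y share an unmeasured cause with loading 0.7 on each, so their within-arm covariance is 0.7 × 0.7 = 0.49. If the programme lowers M by k, the adjusted coefficient of A is 0.49 k:

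- k = 0: simulated estimate 0.00, type I error 0.05
- k = 0.35: formula 0.17, simulated 0.17, type I error 0.37
- k = 0.70: formula 0.34, simulated 0.34, type I error 0.87

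Unadjusted type I error was about 0.05 in all three. With M lowered, the spurious result points towards more utilisation; with M raised, the sign reverses.

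**5. The p<0.1 screen on baseline covariates alone.** Ten candidates, five of them prognostic (assumed r = 0.2), 140 per arm. Screening on outcome: estimate −0.35, type I error 0.052, power 0.89. Screening on arm: estimate −0.35, type I error 0.047, power 0.84. Fixed adjustment for all ten: estimate −0.35, type I error 0.05, power 0.89. No covariates: type I error 0.05, power 0.84. The screen causes no material bias when only baseline variables are eligible.

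**The case against.** The strongest reply is that the named tests are unadjusted, the primary analysis is intention-to-treat, and the sample size rests on an unadjusted contrast, so no regression model can alter that result. This stands. A reader might infer that the rule spoils the trial's primary comparison; the document does not support that. What remains is that the text also commits to a regression and does not rank the two results.

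A second reply is that the data-collection paragraph is conditional and does not say that every listed item will be an adjuster, and that the Data analysis section speaks only of confounders, which a consequence of treatment is not. It is true that the plan does not commit to adjusting for reinfarction or wound infection. But the working definition of a confounder is a univariate screen plus literature and opinion, and none of these excludes a post-randomisation event.

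Third, the harm may be small. Both video consultations follow surgery, so only the preoperative videos could act on duration of surgery or most in-hospital events, and no listed event is named as a target of the programme. This stands as a limit on size. The protocol cannot know in advance, however, that the effect on each variable is nil.

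A reader might also infer that a p<0.1 screen by itself invalidates the adjusted p-values. Step 5 of the working does not bear that out. Nor is this merely detail left to an unseen analysis plan, since the published text itself names the variables and the selection rule.

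Finally, the users-only comparison is not randomised, so real confounding can exist there. A blanket ban on later variables would be too absolute for that analysis.

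**Conclusion.** The point holds as a defect in a stated rule for the adjusted analysis. The list of possible adjusters mixes baseline variables with events that occur after allocation, and the selection rule would readily admit those events. The adjusted estimate could then be biased in either direction, and the text leaves open whether it or the unadjusted result decides.

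The size is not known. Under the assumed linear model, the loss runs from none (programme does not affect the variable) to the whole effect (all of it mediated). The latter needs a shift of 0.70 SD in the mediator, twice the effect for which the trial is sized. It would be wrong to say that the effect will be lost: that follows only if full mediation is assumed, and the documents give neither event rates nor a programme effect on any event. The fault of the p<0.1 screen here is what it lets in, not bias from screening baseline covariates.

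**What to change.** For the intention-to-treat comparison:

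- Adjust only for a short list of variables fixed before randomisation and named in advance, for example age, sex, comorbidities and T0 sociodemographics, plus the T0 score when the outcome is HADS anxiety or SF-36. This list replaces the p<0.1 screen.
- State whether the unadjusted or the adjusted result is decisive for the primary endpoint.
- Report procedural characteristics and follow-up events by arm, as descriptive data or outcomes. If their role in the pathway is of interest, put that in a labelled exploratory analysis.
- Treat the users-only comparison separately, as exploratory and non-randomised, with its own reasoning about confounders.

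This is a change of wording made before the outcome data are analysed. It needs no new data and leaves the sample size as it is. In the check, fixed baseline adjustment left the estimate and type I error unchanged and raised power from 0.84 to 0.89 under the assumed prognostic strength. The cost is the loss of freedom to choose covariates after seeing the data.
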